### Intervention procedure

Each child in the four experimental groups will see and hear a word as spoken by an avatar in the application on their tablet device. The avatar will ask the child to repeat the word. As shown in Figure 1 the “Wizard” will hear the child's response and view a monitor display of the child's screen. The “Wizard” will also see each feedback option on a mobile device and will thus be enabled to immediately assess the utterance and select the appropriate feedback. The child will then see and/or hear the selected feedback as delivered by the avatar in the application.

Each experimental group will receive the same set of words and the same basic presentation of an animal avatar which speaks polite conversational language in a human voice. The words will be presented in random order, rather than a predetermined sequence, to enable children to keep playing as long as they choose. The experimental activity is anticipated to take approximately 10 min. Based on other similar studies in the same laboratory (e.g., Huber et al., 2016) it is not anticipated that most children will chose to play for longer than 20 min. Each word will be spoken by the avatar, simultaneously as it is presented as an image. The avatar will then prompt the child to say the word. The treatment for each group will differ in the context of the presentation and in the feedback delivery as shown Table 4.

### Session schedule

Dosage is a significant variable in intervention for speech sound disorders (Baker, 2012; Kaipa and Peterson, 2016) and relates to the number of treatment sessions, the frequency of treatment sessions, length of treatment sessions and number of trials per treatment session (Baker, 2012). A clear precedent has not been set in the literature as to the most effective or efficacious dosage for phonological therapy, let alone home practice (which the study is aiming to investigate). There is evidence to suggest that treatment should occur three times per week (Allen, 2013) but daily home practice is also used (Crosbie et al., 2005). The number of sessions rarely exceeds 16–21 sessions in total in studies of phonological therapy (Crosbie et al., 2005; Williams, 2012). Despite the novelty of the study in exploring practice with an app the above literature will be used as a guide such that each participant will attend the Swinburne Babylab facility for individual sessions 3–4 days per week over a 2–4 week period for a total of 12 sessions (in addition to testing sessions). As the study seeks to investigate the number of trials (from data on percentage accuracy per trial) and length of session as measures of effectiveness of feedback and motivation, respectively, these parameters of dosage will not be set but we expect that children will engage for up to 20 min completing 80–100 trials.

At the start of the first session children will be evaluated by a qualified speech pathologist with experience in the assessment of children with speech sound disorders to confirm that they fit within the inclusion criteria. This step will be accomplished by collecting a case history and include questions relating to the inclusionary and exclusionary questions as well as previous exposure to speech pathology intervention and speech pathology apps. During this assessment session, the speech pathologist will work through a checklist of instructions which are exemplary of instructions used in the therapy task to ascertain the stimulability of the therapy targets and that the child's comprehension of the instructions to be used in the experimental tasks. Errors in comprehension will be corrected by the speech pathologist within this session. Participants will be randomly assigned to a feedback condition or to the control condition and then take the pre-test. The pre-test and post-test will be offered in a room separate from the Babylab to reduce encoding specificity effects that would provide an advantage to the children in the feedback condition relative to those in the control condition. The control group will attend the first session and then return between 2 and 4 weeks later to take posttest. After completing the pretest, the experimental group will be offered 12 sessions of the experimental activities over a 4-week period. The experimental groups will then be familiarized with the Babylab. Each of sessions two to 12 will consist of approximately 10 min for the experimental task followed by approximately 10 min of an unrelated game or activity for an expected total of 20 min. Children will determine when they want to stop playing the experimental activity. As stated above, the children will complete 80–100 trials of the target minimal pairs but the exact number of trials completed by each child for each session will be recorded and checked for equity between participants. On completion of the experimental task in session thirteen, children will move from the Babylab to take the post-test. See Figure 4 for a diagram of the session schedule.

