**Figure 3 F3:**
[figure not shown]
Study design.

Children will be randomly allocated to one of four experimental groups or to a control group. For type of feedback, verification feedback types KR/MT/RUC are not highly recommended because they do not supply information to guide the learner. However, KR/MT will be included because it is prevalent in multimedia applications, mainly because it is easy to implement. RUC will be excluded because the number of attempts cannot be controlled and because it may inhibit the timely progress of some children. Intrinsic feedback is recommended for multimedia applications because it can assist learning by building upon, and relating to learners' real-world experience (Laurillard, 2002, pp. 58–69; Ke, 2014). We are interested in comparing these two types of feedback in an attempt to verify the value of the less easily implemented intrinsic feedback. KP will also be included because it is arguably the most effective type of formative feedback (Shute, 2008) and also because it is prevalent in speech pathology practice (e.g., Maas et al., 2008). Whereas, KR/MT and intrinsic feedback can be provided alone or in combination with other types of feedback, KP usually follows and elaborates another type of feedback. Consequently, two types of feedback (KR/MT and Intrinsic) will be provided in isolation to highlight their differences and a further two will combine them with KP. The combined KR and KP condition will allow us to more closely simulate speech pathology sessions whereas the combined intrinsic and KP condition is recommended as best practice for multimedia environments. A fifth condition will act as a control for changes in speech development which could occur over time, either naturally or because of other interventions. KCR will not be provided as feedback because it will appear as a prompt when the sound is presented to the child. Table 3 summarizes the rationale behind the choices of types of feedback to be compared in the study. Table 4 presents examples of feedback provided to each experimental group.

**Table 3 T3:** Rationale for feedback type in experimental conditions.

**Group**	**Rationale for use of type of feedback in treatment**	**Feedback type**
1	Prevalent in multimedia applications for speech production because it is easy to implement.	KR/MT

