### Ethics

The protocol was approved by Swinburne University Human Ethics Research Committee: SHR Project 2017/262 on October 20 2017, in accordance with the National Statement on Ethical Conduct in Human Research (2007) and the Australian Code for the Responsible Conduct of Research. The assent of children participating will be sought as well as the consent of a parent or legal guardian as per the NHMRC National Statement Guideline 4.2.7.

The primary operational concern in conducting research into speech sound disorders is the ethical concern of using a non-standard or tested treatment with children. Speech pathology treatments should be characterized by beneficence and non-maleficence yet a non-standard treatment may be of no benefit and delay a child's access to beneficial treatment. The trial described in this protocol avoids these ethical concerns for several reasons. Firstly, the length of this trial is only 3 weeks which is shorter than average waiting list times for speech pathology services (Community Affairs References Committee, 2014) meaning that participation in the trial is unlikely to delay access to standard speech pathology intervention. Secondly, although the need for feedback in speech pathology intervention is accepted by clinicians and adopted into practice, the efficacy of feedback, let alone form or feedback, has not been established in the literature. Some of the treatment conditions in this protocol may expose children to non-standard feedback conditions but without an evidence base for standard practice, non-standard feedback conditions are no less appropriate to use. Thirdly, the treatment conditions proposed are based on sound principles of learning theory and speech pathology practice such that they may be of benefit and are highly unlikely to be of any harm. A final issue is that the control group could be perceived to be disadvantaged as they will not receive the experimental therapy nor traditional therapy during their participation. This is compensated by the fact that they will receive traditional therapy following their participation in the study.

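### The stated durations conflict, and the control group's 2–4 week return is not tied to the roughly 3–4 weeks game children need, so game-versus-control can carry a difference in elapsed time

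*Protocol article*

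**What the plan says.** All references are to the protocol article.

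- **Game groups, first statement (Session schedule):** "3–4 days per week over a 2–4 week period for a total of 12 sessions (in addition to testing sessions".
- **Game groups, second statement (Session schedule):** after the pre-test, "the experimental group will be offered 12 sessions of the experimental activities over a 4-week period".
- **Trial length (Ethics):** "the length of this trial is only 3 weeks". This figure supports the argument that taking part is unlikely to delay standard care.
- **Controls (Session schedule):** "The control group will attend the first session and then return between 2 and 4 weeks later to take posttest".
- **Purpose of the control group (Design):** "A fifth condition will act as a control for changes in speech development which could occur over time", whether natural or due to other interventions.
- **Post-test, game groups (Session schedule):** "On completion of the experimental task in session thirteen, children will move from the Babylab to take the post-test". For sessions 2 to 12 the plan describes "approximately 10 min for the experimental task followed by approximately 10 min of an unrelated game or activity"; no such activity is stated for session 13.
- **Test location (Session schedule):** "The pre-test and post-test will be offered in a room separate from the Babylab to reduce encoding specificity effects".
- **Analysis (Proposed analysis):** the regression uses feedback condition, number of trials, age and severity. The binomial model adjusts for pre-intervention language skills, age and gender, and compares marginal means across all five groups. Neither list contains the time from pre-test to post-test.

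**The concern.** The fifth group is there to show how much speech changes over the same period without the game. It can do so only if its period matches that of the game groups. As written, a control may be re-tested from week 2, while 12 sessions at the stated frequency cannot be finished before week 3. The three statements of duration do not settle which window is meant.

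If controls are on average observed for less time than game children, some ordinary development and some outside help are counted as a game effect. If they are observed for longer, the game effect is understated. The listed models would not adjust for either, and the imbalance cannot be undone after data collection if the interval was not recorded.

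A second, smaller difference is built in. Game children take the post-test after practising target sounds that day, and controls have had no same-day practice. A short-lived gain from the last task cannot then be separated from lasting learning in the game-versus-control contrast.

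**Working it through.** **Inputs.** 12 sessions; 3–4 sessions per week; stated periods of 2–4 weeks, 4 weeks and 3 weeks; control return at 2–4 weeks; pre-test in session 1 and post-test in session 13; 30 children per group in five groups. All are in the protocol article.

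**1. Reproducing the stated 2–4 weeks.** Weeks = sessions ÷ sessions per week.
- At 4 per week: 12 ÷ 4 = 3 weeks.
- At 3 per week: 12 ÷ 3 = 4 weeks.
- Two weeks hold 2 × 3 = 6 to 2 × 4 = 8 sessions; fitting 12 into two weeks needs 12 ÷ 2 = 6 per week.

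The upper end (4 weeks) is reproduced; the lower end (2 weeks) is not. The 4-week statement fits only 3 per week, and the 3-week statement fits only 4 per week.

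**2. Pre-test to post-test in the game groups.** Session 13 falls 12 session-steps after session 1. Placed on a calendar, it is day 21 at 4 per week and day 28 at 3 per week, or 3.0–4.0 weeks.

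**3. Difference in interval, game minus control.**
- Smallest: 3 − 4 = −1 week.
- Largest: 4 − 2 = +2 weeks.
- Control returns spread evenly over 2–4 weeks (assumption) have mean 3 weeks. The mean gap is then 3 − 3 = 0 to 4 − 3 = 1 week.
- Both groups at mid-range: 3.5 − 3 = 0.5 week.

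**4. What the gap could do.** Bias = weekly natural change × mean gap in weeks. The document gives no weekly rate, so 0.02–0.10 SD per week is **assumed** for illustration. With a two-sided 5% z-test, the chance of rejecting when the game has no effect is 1 − Φ(1.96 − d/SE) + Φ(−1.96 − d/SE), where d is the bias in SD units. SE = √(1/30 + 1/30) = 0.258 for one game arm against control, and √(1/30 + 1/120) = 0.204 for the four game arms pooled.

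| Mean gap | Bias (SD) | Type I error, 30 v 30 | Type I error, 30 v 120 |
|---|---|---|---|
| 0.5 week | 0.01–0.05 | 5.0–5.4% | 5.0–5.7% |
| 1 week | 0.02–0.10 | 5.1–6.7% | 5.1–7.8% |
| 2 weeks | 0.04–0.20 | 5.3–12.1% | 5.4–16.5% |

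The last row requires every control to return at 2 weeks and every game child to finish at 4, so it is a bound, not an expectation.

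**5. Recency.** No arithmetic applies. The post-test is placed on completion of the session-13 task. The unrelated activity is described for sessions 2–12 only. The separate room deals with where the child is tested, not with how recently the child practised.

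**The case against.** The strongest reply is that the protocol intends matching windows: it gives 2–4 weeks both to the game course and to the control return. On that view the only fault is a lower bound that does not fit the frequency, and if the 2–4 week period governs, the nominal windows coincide. This is fair. The confounding is possible, not established, and it depends on which of two conflicting statements holds. The windows also overlap throughout weeks 3–4. What stands is that the text does not say which statement governs and does not tie a control's return to the interval of game children.

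Four stronger readings are tempting but not supported.

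- **That elapsed time always favours the game.** A control returning at week 4 against a game child finishing at week 3 biases the other way.
- **That the schedule contradicts itself on testing sessions.** Session 1 holds assessment and pre-test, and sessions 2–13 are twelve game sessions. Testing is thus additional to the 12, and nothing implies a separate post-test visit.
- **That arriving from the Babylab reveals the arm to the assessor.** Recruitment of participants states that the assessor is blind to condition, and nothing says the assessor sees where a child comes from.
- **That the comparison of feedback types is damaged.** All four feedback groups share one schedule and one post-test arrangement.

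On recency, the plan does show awareness that test conditions could advantage game children, and it moves the tests to another room. The DEAP is also meant to capture generalization and is not the game's own trial score. Any immediate practice effect is therefore plausible but unquantified. The schedule diagram (Figure 4) is not shown and may clarify the timing, although it could not remove the conflict between the written statements.

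**Conclusion.** The point holds in a limited form. The durations (2–4 weeks, 4 weeks, 3 weeks, and 12 sessions at 3–4 per week) cannot all be right. At the stated frequency, controls can be post-tested earlier than any game child who completes the course. The interval difference ranges from −1 to +2 weeks, with a mean of about 0–1 week if control returns are evenly spread.

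The resulting bias in game-versus-control is unknown because no maturation rate is given. Under the assumed 0.02–0.10 SD per week it is small at mid-range (0.01–0.05 SD, type I error at most about 5.7%). It matters only if the gap approaches its extreme. The difference in practice recency does not depend on that rate: it applies to every game child tested as described, and its size cannot be derived from the document. Contrasts among the four feedback arms are not affected.

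The change is worth making because it is inexpensive and an unequal, unrecorded interval cannot be repaired later.

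**What to change.** 1. Reconcile the statements in Session schedule and Ethics to one schedule. Which number of sessions, frequency or period is right is for the investigators to decide.
2. Give controls the same pre-test-to-post-test window as the game arms. One way is to schedule each control's return to the planned interval of game children in the same severity stratum.
3. Record the actual interval for every child, so that balance can be checked and the interval used in a sensitivity analysis.
4. For recency, choose one of two options. Either place a practice-free gap between the session-13 task and the post-test, such as the unrelated activity already used in sessions 2–12, or state that the game-versus-control contrast includes any immediate practice effect.

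The cost is wording, appointment planning for the 30 controls, one recorded variable and, if the gap is chosen, a few minutes in the final session. A separate post-test visit is not asked for: it would add up to 4 × 30 = 120 child visits, which this concern does not clearly justify.

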### Outcome measurement

The relative benefits of the different experimental conditions will be measured by the primary measure of changes in use of phonological processes and PCC from pre-test to post-test as measured by the DEAP (Dodd et al., 2002). Such assessment will capture suppression of the phonological processes targeted in treatment and generalization effects (if any) to other phonological processes. Phonological process percentage of occurance (Randolph and Wendt, 2014; i.e., the number of times that a child uses a given phonological process) will also be measured and compared pre and posttest. Pre and post-test assessments will be recorded and a sample of the assessments independently analyzed followed by interrater reliability checks. In addition to the pre-test/post-test measures, number of trials and percentage accuracy of trials per session (cumulative accuracy) will be measured for each experimental condition as further indication of the effectiveness of feedback of that condition and determine when goals of intervention have been reached. For example, if a child reaches 90% accuracy of production of target words for one phonological process, another will be targeted. It could be argued that motivation to continue playing will increase practice and consequently improve outcomes (Williams, 2012). A secondary measure of motivation as a variable that could influence the effectiveness of feedback type will be the amount of time participants choose to continue playing the game (Deci et al., 1999) up to a total of 20 min as well as the number of trials they complete.

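### The post-test is tied to completing session thirteen in the four game groups but to the calendar in the control group, which leaves game-versus-control comparisons open to unequal loss and unequal elapsed time

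*Protocol article*

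**What the plan says.** All the relevant text is in the protocol article, mostly under Session schedule.

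- **Order of events.** "Participants will be randomly assigned to a feedback condition or to the control condition and then take the pre-test". Any later loss is therefore loss after randomisation.
- **Game groups, sessions.** "After completing the pretest, the experimental group will be offered 12 sessions of the experimental activities over a 4-week period". The same section also describes "individual sessions 3–4 days per week over a 2–4 week period for a total of 12 sessions (in addition to testing sessions").
- **Game groups, post-test.** "On completion of the experimental task in session thirteen, children will move from the Babylab to take the post-test".
- **Control group, post-test.** "The control group will attend the first session and then return between 2 and 4 weeks later to take posttest".
- **Primary measure (Outcome measurement).** It consists of "changes in use of phonological processes and PCC from pre-test to post-test as measured by the DEAP", so a child without a post-test has no primary outcome.
- **Stopping play.** "Children will determine when they want to stop playing the experimental activity". In context this is a choice made within a session; Outcome measurement uses playing time, capped at 20 minutes, as a measure of motivation.

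The Design section says that the control group is there to account for change in speech over time, whether natural or due to other interventions. The sample-size paragraph in Proposed analysis gives 30 children in each of 5 conditions and mentions no allowance for loss. The Session schedule figure is not available in the text reviewed.

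**The concern.** A control group accounts for change over time only if its outcome is collected in the same way, and after a similar interval, as in the groups it is compared with. Here the two rules differ in kind. A game child reaches the post-test by attending; a control reaches it by the passing of time. Two consequences follow if the schedule is applied as written.

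First, game children who miss later sessions or leave the study could lack a post-test, while the control schedule asks for one return visit only. If the children who fall away are those who would have improved less, the game groups' observed mean change is too high and the comparison with control is flattered. If they are those who would have improved more, the bias runs the other way.

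Second, the interval between pre-test and post-test may be shorter for controls. Children aged 4 to 6 can improve without treatment, so a shorter control interval gives less room for natural change and again favours the game.

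A larger sample cures neither problem, and an analysis plan cannot recover an assessment that was never scheduled.

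**Working it through.** **1. Visits needed to reach the post-test**

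- Control: session 1 + 1 return = 2 visits.
- Game: session 1 (eligibility and pre-test) + 12 game sessions = 13 visits, which agrees with the numbering of session thirteen.

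**2. Elapsed time**

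- At 4 sessions per week: 12 / 4 = 3 weeks. At 3 per week: 12 / 3 = 4 weeks.
- In 2 weeks at 4 per week: 2 × 4 = 8 sessions, short of 12. The lower end of the stated 2 to 4 week period cannot be met at the stated frequency.
- The control window opens at 2 weeks. A control tested then is tested about 1 to 2 weeks earlier than game children. A control tested at 3 to 4 weeks is matched.
- The documents give no rate of untreated improvement, so I do not put a size on this part.

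**3. How likely is it that a child falls short of 12 sessions?** (attendance rates are assumed, and sessions treated as independent)

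- With exactly 12 slots (3 per week for 4 weeks), all 12 are attended with probability p^12: 0.90^12 = 0.28; 0.95^12 = 0.54; 0.98^12 = 0.78.
- With the 16 slots that 4 per week for 4 weeks would allow, the probability of attending at least 12 of 16 (binomial) is 0.98 at p = 0.90 and 0.999 at p = 0.95.
- Scattered absences are therefore largely absorbed if make-up slots are used. The loss that remains a concern is drop-out from the visit schedule.

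**4. The plan's sample size, and power after loss**

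The stated total is 150 for f = 0.32, 5% significance and 80% power. For a one-way F test on 5 groups (noncentrality N × f², df 4 and N − 5), I obtain 122, or 125 with equal groups, so I do not reproduce 150. It lies above the requirement and gives 88.8% power. With loss in the four game groups only, N = 30 + 120 × (1 − loss):

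| Loss in game groups | N | Power at f = 0.32 |
|---|---|---|
| 0% | 150 | 88.8% |
| 10% | 138 | 85.6% |
| 20% | 126 | 81.7% |
| 30% | 114 | 77.0% |

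Power holds up to about 20% loss. The issue is bias.

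**5. Size of the bias** (loss rate d and correlation r are assumptions)

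Assume no true effect, no loss in control, and a normal latent tendency to complete that correlates r with the outcome. The completers' mean then shifts by r × φ(z_d) / (1 − d) standard deviations.

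- d = 10%: φ(−1.282) / 0.9 = 0.1755 / 0.9 = 0.195. r = 0.2 to 0.5 gives 0.04 to 0.10 SD.
- d = 20%: 0.2800 / 0.8 = 0.350, giving 0.07 to 0.18 SD (0.175 before rounding).
- d = 30%: 0.3477 / 0.7 = 0.497, giving 0.10 to 0.25 SD.

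Dividing the shift by the standard error of the difference gives the actual error rate of a nominal two-sided 5% test. The standard error is √(1/30 + 1/(30(1 − d))) for one game group against control, and √(1/30 + 1/(120(1 − d))) for the four pooled:

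| Loss | One game group vs control | Four game groups pooled vs control |
|---|---|---|
| 10% | 5–7% | 5–8% |
| 20% | 6–10% | 6–13% |
| 30% | 6–14% | 8–22% |

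**The case against.** The strongest reply is that the session-thirteen sentence merely describes where a child who is on schedule goes next. A reader might infer that game children who miss sessions are never followed up. The text does not say so: it states no exclusion or withdrawal rule, the schedule figure is not shown, and follow-up of non-completers may be set out in the full protocol or analysis plan. That inference is not supported, and I do not make it.

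Four further points stand:

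- Stopping play early is a within-session choice and an intended measurement. A child who plays briefly at every visit still reaches session thirteen and is tested.
- A visit-based trigger has no calendar cut-off, so a child who merely runs late does not lose the post-test.
- The trigger is the same in all four game groups, so the schedule builds no asymmetry into the feedback-type contrasts. The article predicts that the intrinsic conditions will be more motivating, but it measures this by trials and playing time and says nothing about attendance.
- The 28%, 54% and 78% completion figures apply only if there are no make-up slots. They should not be read as forecasts.

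What the reply does not remove is the difference between the two rules. Both are stated in the article: one depends on attendance, the other on elapsed time, and the control window opens before a game child on the stated frequency can have finished.

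**Conclusion.** The point holds for comparisons of the game groups with control. As written, the primary pre-to-post change is collected by attendance after 13 visits in four groups and by calendar after 2 visits in the fifth, and controls may be tested up to about 2 weeks earlier. This opens the comparison to differential loss after randomisation and to unequal time for natural change.

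The size of the loss bias cannot be read from the documents. It is small (0.04 to 0.10 SD) if 10% of game children are lost, and material (0.10 to 0.25 SD) if 30% are, given an assumed correlation of 0.2 to 0.5 between completing and outcome. A positive correlation, and so a bias in favour of the game, is itself an assumption. Contrasts between feedback types are distorted only if attendance differs by type, which the documents do not establish.

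**What to change.** - Set one post-test window, counted in calendar time from the pre-test and identical for all five groups. Make it long enough to contain the 12 offered sessions, and reconcile it with the differing durations now in the article (2 to 4 weeks and 4 weeks under Session schedule, 3 weeks under Ethics).
- State that every randomised child is invited to that post-test whatever the number of sessions attended, and is analysed in the allocated group.
- Record the number of sessions attended by each child.

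The cost is a few sentences of protocol text, since one post-test per child is already planned. It should be settled before enrolment, because a missed assessment cannot be recovered. The small downside is that some game children will be tested after fewer than 12 sessions, so the estimate becomes the effect of offering the game and not of completing it.
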